### Statistical analysis

Descriptive statistics will be performed to ensure comparability between scores at baseline as well as to test the assumption of homogeneity of variance for use of parametric statistics. To evaluate the effect of the intervention, mixed models (SPSS Inc., Chicago, IL, USA) with an alpha level of 0.05 will be used where appropriate. Significance of main or interaction effects will be explored using the Bonferroni post hoc test. In case of skewed distributed data, logarithmic transformations or corresponding non-parametric statistics will be used to assess main effects of the intervention.

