### Randomisation

Participants will be divided into two geographic cohorts (south and north) to reduce the travelling time for the participants. After baseline assessments, the participants in each cohort will be randomly assigned to two different groups in blocks of four, one experimental group with balance training and one control group. The sequence of allocation will be performed using web-based software and will be concealed to the participants and testers until the baseline measurement is completed. Blinding of group allocation will, however, not be possible since the test leaders will be supervising the training intervention (as described below).

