### Sample size

The sample size for this study was determined from a pilot study (not yet published), including five mild to moderate PD subjects who participated in the proposed balance training, and also from previous trials on patients with PD and elderly people
[53,73,74]. For each sample size calculation, power was set at 80% and a two-sided test at the alpha level of 5%. For the Mini-BESTest, a sample size of 24 was required to detect a 3-point difference between groups, assuming a mean variance or standard deviation (SD) of 3.6 (effect size: 0.83). For the interference effect of dual task performance, i.e. percent change in gait velocity (m/s) between single and dual task walking
[74], a sample size of 27 subjects was required to detect a difference of 10% (SD 13) between groups (effect size = 0.77). Finally, for the FES- I, a sample size of 32 subjects was required to detect a difference of 2 points (SD 2.8) between groups (effect size = 0.71). The dropout rate was set at 15%, corresponding to intervention studies with PD subjects
[75,76]. Taken together, to ensure adequate statistical power the sample size for this study would optimally be 40 per group (total n = 80).

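### The analysis states no baseline covariate and no cohort term, and checks baseline comparability instead; prespecifying both is valid, cheap and usually more precise

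*Protocol article*

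**What the plan says.** Three parts of the protocol article bear on this.

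- **Statistical analysis.** Baseline appears once, as a check: "Descriptive statistics will be performed to ensure comparability between scores at baseline". The treatment effect is then assessed with mixed models, in which main or interaction effects are examined with Bonferroni post hoc tests. For skewed data the section allows a log transformation or a non-parametric method for the main effects of the intervention. No fixed effects or covariates are listed.
- **Randomisation.** Patients are split into a south and a north cohort, and "the participants in each cohort will be randomly assigned to two different groups in blocks of four". Cohort is therefore a stratification factor.
- **Outcome measures and test procedure.** Both groups are assessed before the intervention, after the 10 weeks, and at 9 and 15 months after entry. Each patient is thus due a baseline value and three later values.

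For the size of the effect, the Sample size section gives the FES-I assumptions: "a sample size of 32 subjects was required to detect a difference of 2 points (SD 2.8) between groups (effect size = 0.71". It does not say whether 2.8 is the SD of follow-up scores or of change scores.

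**The concern.** Describing the groups at baseline can show an imbalance but cannot prevent or correct one. Any imbalance after proper randomisation is due to chance, and the efficient response is to condition on the baseline value in a model fixed in advance.

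The only stated role for baseline is this check. With four assessments and a test of main or interaction effects, the likely model is group, time and group-by-time, with baseline as the first response. Two costs follow:

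- The group-by-time contrast from baseline behaves like a change-score comparison, which is less precise than a baseline-adjusted one unless the correlation is very high.
- A group main effect averaged over all visits includes one visit where the true difference is zero, so it is diluted.

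The cohort is used in the design, but the analysis text does not mention it. If outcomes differ between cohorts, the unadjusted standard error is too large. At stake are precision and a clear estimand for three primary outcomes, not the validity of the trial.

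**Working it through.** **Inputs from the Sample size section.** "For each sample size calculation, power was set at 80% and a two-sided test at the alpha level of 5" per cent; FES-I difference 2, SD 2.8; dropout 15%; 40 per group.

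**Assumed.** Rho, the correlation between baseline and follow-up (not given; range 0.3 to 0.7), equal SDs at the two times, and R², the share of outcome variance due to cohort (not given; 5% to 10%).

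**1. The plan's own figures.** The standardised differences are 3/3.6 = 0.83, 10/13 = 0.77 and 2/2.8 = 0.71. A two-sample t-test at 80% power needs 24, 28 and 32 per group. The normal approximation gives 23, 27 and 31. The stated 24, 27 and 32 reproduce when read as per group. After dropout, 40 × 0.85 = 34 per group remain. FES-I power at 34 per group, with no adjustment and SD 2.8, is 0.83.

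**2. Variance of the treatment contrast at one follow-up visit, in units of the follow-up variance.**

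- Change from baseline: 2(1 − rho)
- Baseline-adjusted: 1 − rho²
- Ratio, adjusted to change: (1 − rho²)/[2(1 − rho)] = (1 + rho)/2

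The ratio is 0.65, 0.75 and 0.85 at rho = 0.3, 0.5 and 0.7. Adjustment therefore removes 35%, 25% and 15% of the variance.

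**3. FES-I power, 34 per arm, t-test.** If 2.8 is a follow-up SD, the effective standardised difference is 0.714/√[2(1 − rho)] for change and 0.714/√(1 − rho²) when adjusted. If 2.8 is a change-score SD, it is 0.714 for change and 0.714/√[(1 + rho)/2] when adjusted.

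| rho (assumed) | Follow-up SD: change → adjusted | Change-score SD: change → adjusted |
|---|---|---|
| 0.3 | 0.69 → 0.86 | 0.83 → 0.95 |
| 0.5 | 0.83 → 0.92 | 0.83 → 0.92 |
| 0.7 | 0.96 → 0.98 | 0.83 → 0.88 |

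Example at rho = 0.3, follow-up SD: change 0.714/√1.4 = 0.604, power 0.69; adjusted 0.714/√0.91 = 0.749, power 0.86.

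**4. Dilution of a group main effect.** Suppose the true effect is the same, D, at all three follow-ups and zero at baseline. The average over four visits is (0 + D + D + D)/4 = 0.75 D. If the effect is present only after the 10 weeks, it is D/4, against D/3 when only post-baseline visits are averaged.

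**5. Cohort.** Omitting it inflates the standard error by 1/√(1 − R²): 1.026 at R² = 5% and 1.054 at 10%. A simulation of 80 patients (40 per cohort, blocks of four within cohort, 10,000 runs) gave these type I error rates:

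| Cohort difference | Cohort ignored | Cohort adjusted |
|---|---|---|
| 0 SD | 4.9% | 4.9% |
| 0.5 SD | 4.3% | 5.0% |
| 1 SD | 3.1% | 5.2% |

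Ignoring cohort is conservative and does not inflate error.

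**The case against.** The strongest reply is that this reads too much into silence. The article lists no model terms, so it excludes neither baseline nor cohort, and covariate lists are often left to a fuller document. A longitudinal mixed model with baseline as a response is standard and valid. If it constrains the baseline means to be equal, adding a baseline covariate gains almost nothing. The planned sample size reproduces without adjustment, and 34 per group still gives 0.83 for FES-I on the plan's own two-group calculation. The cohorts were formed to shorten travel, and nothing suggests that geography predicts outcome.

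Much of this stands, and it limits the point to efficiency. It does not remove it. The section does state a purpose for the baseline check that the check cannot serve, and what it goes on to state gives baseline no covariate role. The 0.83 assumes a comparison with SD 2.8; if that is a follow-up SD and rho is 0.3, the change contrast has 0.69.

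A reader might also infer three stronger things, which the document does not support:

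- *That patients are not analysed as randomised.* Nothing departs from analysis by assigned group; one stratification factor is simply not named.
- *That the model will be chosen after looking at baseline.* No modelling choice is tied to the comparability check. The conditional rules concern variance and skewness.
- *That baseline imbalance passes straight into the estimate.* In a change contrast the baseline is subtracted. Given an imbalance, what remains is (1 − rho) times it, with opposite sign, and the estimator is unbiased over randomisations.

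**Conclusion.** The point holds as one of efficiency and wording. The stated purpose of the baseline check is wrong, and the analysis as naturally read is valid but gives away precision. For a single-visit contrast the variance saving is 35% to 15% over rho = 0.3 to 0.7. For FES-I, adjustment adds 2 to 17 percentage points of power if 2.8 is a follow-up SD, and 5 to 12 if it is a change-score SD. Adjustment gains under both readings and at every rho shown, and the variance saving shrinks as rho rises. Only the follow-up reading with low rho takes the change contrast below the 80% target.

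The figures rest on assumed rho, equal SDs at baseline and follow-up, 34 per arm, and a model that does not already constrain baseline means to be equal. Leaving out cohort costs about 3% to 5% in standard error if cohort explains 5% to 10% of the variance, and nothing if it explains none. It makes the test at most conservative.

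**What to change.** In the Statistical analysis section:

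1. Replace the aim of ensuring comparability with a plain description of baseline data by group.
2. For each outcome, prespecify a mixed model with the post-baseline visits as response and fixed effects for group, visit, group × visit, baseline value of that outcome, baseline × visit, and cohort (south/north). With baseline out of the response, no group effect is averaged over a visit where the true difference is zero.
3. Keep the baseline and cohort terms when an outcome is log-transformed. The skewed-data route as now worded mentions no adjustment.

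This is a change of wording before analysis. It uses data already planned for collection, needs no more patients, and costs a few degrees of freedom.

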### Sample size

The sample size for this study was determined from a pilot study (not yet published), including five mild to moderate PD subjects who participated in the proposed balance training, and also from previous trials on patients with PD and elderly people
[53,73,74]. For each sample size calculation, power was set at 80% and a two-sided test at the alpha level of 5%. For the Mini-BESTest, a sample size of 24 was required to detect a 3-point difference between groups, assuming a mean variance or standard deviation (SD) of 3.6 (effect size: 0.83). For the interference effect of dual task performance, i.e. percent change in gait velocity (m/s) between single and dual task walking
[74], a sample size of 27 subjects was required to detect a difference of 10% (SD 13) between groups (effect size = 0.77). Finally, for the FES- I, a sample size of 32 subjects was required to detect a difference of 2 points (SD 2.8) between groups (effect size = 0.71). The dropout rate was set at 15%, corresponding to intervention studies with PD subjects
[75,76]. Taken together, to ensure adequate statistical power the sample size for this study would optimally be 40 per group (total n = 80).

## Discussion

In this study protocol, a conceptual framework based on current scientific knowledge from neuroscience constraints in PD is used to design a training intervention targeting balance and walking performance in PD. The rationale for this training approach relies on findings of preserved motor learning in mild to moderate stages of PD
[51] and the plausibility of training-induced neuroprotection
[14,15]. Although previous exercise interventions in PD have reported promising results for balance and gait performance
[16-18], they often lack to report the underlying principles of the intervention
[21]. In particular, knowledge concerning the influence of active elements of the intervention (e.g. exercise components, training dosage and intensity) is limited
[21]. In contrast to the majority of previous training regimes that emphasise general physical training
[17] or target single physiological systems (e.g. muscular strength, reactive postural adjustments), the active elements in this intervention cover traditional training principles of specificity, progressive overload and random training. Hence, these principles are modified to promote motor learning in PD through specific balance components related to PD symptoms during highly challenging and varying exercise conditions. There is an urgent need to investigate both short-term and long-term effects of new exercise strategies targeting balance control in PD
[17].

Balance impairment in PD comprises a wide spectrum of disability and health
[16]. Detailed long-term follow-up, 1 year post-intervention, in the proposed study will give a unique opportunity to address important questions concerning potential effects of and limitations for group-based balance training. First of all, the proposed study will be one of the first trials to provide knowledge of potential effects of exercise intervention according to the whole spectra of ICF domains, including laboratory measurements, clinical tests, and free-living and self-perceived assessments (see Table
3). Such knowledge will be essential for designing and improving exercise interventions in the future. Secondly, long-term follow-up will provide knowledge of the maintenance of potential training effects. This is particularly important for PD given the progressive deterioration of the disease in which regular periods of supervised balance training may be required to sustain physical performance.

Since this intervention will not be restricted to a fixed program with specific exercises, several steps will need to be taken to standardise the intervention by educating physiotherapists in the framework and implementation of the training approach, as well as supervising the physiotherapists during the course of training and monitoring training performance as well as progression. During the course of training, each training session is planned with regard to the different phases of the intervention (see Table
2) and adapted by the physiotherapist to meet individual capacities of the participants. The physiotherapists conducting the training will be responsible for transferring the conceptual framework into practice, using a pragmatic approach rather than restricting the intervention to a standardised protocol. Thus, translation of this research intervention into the clinical setting will be enhanced.

There are several limitations to the proposed study. The result of this intervention can only be generalised to individuals with mild to moderate PD
[45] and group training in outpatient care. All measurements will be conducted at the same time of the day during the ON phase of levodopa medication. The total dose of medication will be monitored in a longitudinal perspective
[77], though separating the potential effects of balance training from those of levodopa medication will be limited. Moreover, blinding of the test leaders will not be possible since they also will serve as support for the physiotherapists conducting the intervention. However, this proposed randomised controlled trial has the potential to provide new knowledge and a change in focus concerning balance interventions in PD.
